# Usual care including home exercise with versus without spa therapy for chronic low back pain: protocol for the LOMBATHERM’ study, a multicentric randomised controlled trial

**DOI:** 10.1186/s13063-020-04271-9

**Published:** 2020-05-11

**Keywords:** Crenobalneotherapy, Underwater massages, Mud application, Water exercises, Low back pain, Spa therapy

## Abstract

**Background:**

Low back pain is highly prevalent and a major source of disability worldwide. Spa therapy is frequently used to treat low back pain, but the associated level of evidence for efficacy is insufficient. To fill this knowledge gap, this protocol proposes an appropriately powered, prospective, evaluator-blinded, multi-centre, two-parallel-arm, randomised (1:1), controlled trial that will compare spa therapy in addition to usual care including home exercise (UCHE) versus UCHE alone for the treatment of chronic low back pain.

**Methods:**

Eligible patients (anticipated sample size of 358) will have had low back pain for more than 3 months and scores for pain greater than 40 mm on a visual analogue scale (VAS). Following initial consent for UCHE and baseline evaluations, patients are randomised (1:1) to UCHE alone, or UCHE plus spa therapy (18 days of mud packs, underwater massages, showers and water exercises under medical supervision). Patients in the latter arm will be requested to sign an additional consent form as per Zelen randomisation. Follow-up visits will occur at approximately months 1, 6 and 12 and (along with baseline assessments) will cover changes over time in VAS pain scores, the impact of lower back pain on daily life (the Rolland and Morris Disability Questionnaire (RMDQ)), inappropriate fears and beliefs about lower back pain (the fear, avoidance, belief questionnaire (FABQ)), general quality of life (the Euroqol Group 5 dimension, 5 level questionnaire (EQ-5D-5 L)), Patient Acceptable Symptom State (PASS), consumption of analgesic drugs and nonsteroidal anti-inflammatory drugs (NSAIDs), and overall state of health. Health resource use and days of sick leave (and subsequently the associated costs) will also be recorded. The primary outcome is the presence/absence of a clinically relevant change (improvement of at least 30%) in the VAS score for pain at 6 months.

**Discussion:**

Despite the fact that previous, rather dated recommendations encourage spa therapy for the treatment of low back pain, the current literary corpus is methodologically poor. This protocol has been designed to provide results spanning a thorough range of outcomes at the highest evidence level possible.

**Trial registration:**

ClinicalTrials.gov: NCT03910023. Registered on 10 April 2019.

## Background

Chronic low back pain is a common complaint. It is estimated that about 80% of people will experience lumbar pain at some point in their lives [1]. Epidemiological studies show an increase in the prevalence of chronic low back pain (from 3.9% in 1992 to 10.2% in 2006 in the American population [2]). In a study conducted in 2010, it was estimated that the frequency of low back pain was in sixth place out of the 271 conditions studied, with a prevalence of 9.4% and it was the first cause of disability in the world with 58.2 million disability-adjusted life years (DALYs: number of years lived with a disability) [3].

As concerns treatments, the medications most often prescribed for chronic low back pain pose various problems. Analgesics, recommended as the first line of therapy in most clinical practice guidelines, have limited efficacy that was even considered negligible and insignificant in a recent review [4]. Nonsteroidal anti-inflammatory drugs (NSAIDs) are associated with poor digestive and renal tolerance during long-term use. Opioids have well-documented short-term efficacy, but their long-term efficacy is uncertain, they are sometimes poorly tolerated by older patients, and their long-term use is complicated by addiction in 24% of cases [5, 6].

Given the variable inefficacy of pharmaceutic treatments, different types of physical therapy are an important part of the therapeutic arsenal for low back pain. There have been several trials of spa therapy as one such alternative, which is now recommended for the treatment of chronic low back pain [7, 8]. The latter publications mainly included three studies by a team from Nancy, France that were implemented in the 1990s [9–11]. A systematic review on the subject has been recently published [12], underlining numerous methodological limitations: a lack of primary outcome, failure to perform an intention-to-treat analysis, or no attempt at evaluator blinding. Additionally, certain studies had a waiting list design that could overestimate the effect of the spa treatment. Nevertheless, review studies conclude that spa therapy as part of a multifactorial treatment regimen can improve pain, function, drug consumption and sometimes quality of life [12, 13]. The best level of evidence, however, is still provided by studies conducted in the 1990s.

We propose to fill this methodological/knowledge gap by implementing a trial with the highest level of evidence possible. Our working hypothesis is that spa therapy in addition to usual care including home exercises (UCHE) will result in greater improvements in pain reduction, associated disability and quality of life in patients with chronic low back pain. It follows that health resource consumption and related costs should also be reduced. The primary objective of this study is therefore to compare the therapeutic effect of UCHE alone versus spa therapy in addition to UCHE for chronic low back pain (Fig. 1). Secondarily, we will also (1) evaluate the therapeutic effects specific to each spa centre, (2) specifically describe effects among subjects who are currently engaged in a professional activity, (3) evaluate treatment tolerance and (4) evaluate per-patient health resource use and associated costs.

**Fig. 1 Fig1:**
[figure not shown]
The LOMBATHERM’ trial flow chart. Usual care including home exercise (UCHE) alone will be compared with UCHE plus spa therapy with assessments at 1, 6 and 12 months

## Methods/design

### Trial design

In this prospective, evaluator-blinded, multi-centre, two-parallel-arm, Zelen randomised (1:1) controlled trial, we will compare UCHE alone with spa therapy in addition to UCHE for the treatment of chronic low back pain (Fig. 1).

### Study setting and population

This study will take place in and around well-established spa centres in Europe (see Table 1). Patients living within a 30-km radius of a participating spa centre and meeting eligibility criteria (Table 2) may participate. Recruitment, enrolment and follow-up visits will occur outside of spa centres (and independent thereof) in participating private offices/clinics, public general hospitals and public university hospitals. The single-payer system in France, where most of the participating spa centres are located, offers medical care to all citizens and residents, and the study population should thus represent a wide range of socioeconomic and rural versus urban backgrounds.

**Table 1 Tab1:** Participating spa centres

Name	Nearby city, Country
Aix-les-Bains	Chambéry, France
Amnéville	Metz, France
Balaruc les Bains	Montpellier, France
Dax	Bayonne, France
Evico Terme	Trentino, Italy
Greoux les Bains	Aix en Provence, France
Hervideros de Cofrentes	Valencia, Spain
Jonzac	Bordeaux, France
Royat	Clermont Ferrand, France
Russian Research Center for Medical Rehabilitation and Balneology	Moscow, Russian Federation
Saint Amand les Eaux	Valenciennes, France
Saint Paul lès Dax	Bayonne, France
Saline Cacica	Northeast Romania
Széchenyi Bath	Budapest, Hungary

**Table 2 Tab2:** Inclusion and exclusion criteria for participants

Inclusion criteria	Exclusion criteria
Adult patient presenting with chronic low back pain: usual pain of the lumbar region lasting for more than 3 months. This pain may radiate to the buttocks, iliac crest, and does not go past the knee [7]	Patients with specific low back pain
Patient presenting upon inclusion with a current pain intensity on a visual analogue scale (VAS) > or = 40 mm.	Patients with severe depression, psychosis
The patient has signed the informed consent form	Patients who have already had a spa treatment in the previous 6 months
Subject aged over 18 and under 80 (years)	Patients with a contraindication for spa treatment^a^
The patient is a beneficiary of a social security programme (national health insurance)	Patients with a professional activity related to balneotherapy (to avoid any conflict of interest)
	Patients with cruralgia or sciatic pain beyond the knee
	Other treatments that may interact according to the investigator’s judgement
	Patients who live more than 30 km away from the spa^b^

^a^ Immune deficiency, progressive heart disease, progressive neoplasia, infection, chronic bronchitis [14] or foreseeable intolerance to thermal care (intolerance to heat, baths, swimming pool, etc.)

^b^ It will not be convenient to make patients travel more than 60 km per day in their vehicle to deliver between 1 h and 1 h 30 min of outpatient care

In general, eligibility criteria (Table 2) are designed to select for patients with chronic low back pain with a certain level of minimum pain while ruling out cases of specific low back pain. In the case of suspicion of the latter, patients will be aetiologically assessed for rule-out.

### Interventions and study arms

Two interventions are implemented during this trial (Fig. 1): (1) usual care including a home-exercise programme (UCHE) and (2) spa therapy. The UCHE intervention is designed to be a comparator arm that represents standard care, while limiting care heterogeneity. Patients assigned to the control arm of the study will have the UCHE intervention only, and those assigned to the experimental arm will have both the UCHE intervention and the spa therapy intervention.

The UCHE intervention will correspond to current practice (including the continuation of previous treatments, if applicable) as decided by the patient’s general practitioner. They will also be provided with a practical guide on how to manage back pain (the “back book”), including a recommended home exercise programme [15]. The practical guide on back pain and the exercise programme [15] will be presented to the patient by the recruiting investigators during the enrolment visit and prior to randomisation. Use of the “back book” and daily home exercises will be requested of patients and encouraged throughout the study (Table 3); home exercise observance will be queried at each follow-up visit (Table 3) by asking the patient on what days during the previous week he/she performed the required exercise routine. The recruiting investigator will further encourage and insist that all study participants are to keep trial participation a secret from evaluating investigators.

**Table 3 Tab3:** The LOMBATHERM’ protocol schedule for enrolment, interventions, assessments, and visits for participants

Visit/event:	Enrolment visit^a^		Intervention period	Follow-up visits^b^		
	Baseline	Allocation		1	2	3
Target chronology (days, weeks, months)	D0	D0 (after baseline)	D1–D60	M1^c^ (D28–D60)	M6 ± 4 W	M12 ± 4 W
**Enrolment and allocation**						
First study presentation and consent 1	✓					
Randomisation		✓				
For those patients randonmised to the experimental arm, presentation of additional spa-treatment and consent 2		✓				
**Interventions**						
Explanation about low back pain and home exercise training for all patients	✓					
Daily exercises at home using the “back book” for all patients^d^			*Throughout intervention and follow-up periods*			
Eighteen consecutive days of spa-therapy (except Sundays) for patients in the experimental arm			✓			
**Observance**						
Home exercise observance				✓	✓	✓
Spa therapy observance (experimental arm only)			✓			
**Harms**						
Tolerance: adverse event characterisation and reporting			*Throughout intervention and follow-up periods*			
**Assessments**						
Demographics and disease history^e^	✓					
Visual analogue scale for low back pain	✓			✓	✓	✓
The Rolland and Morris (RMDQ) scale	✓			✓	✓	✓
The FABQ	✓			✓	✓	✓
The EQ-5D-5L questionnaire	✓			✓	✓	✓
Patient Acceptable Symptom State	✓			✓	✓	✓
Global opinions on state of health^f^	✓			✓	✓	✓
Drug consumption in the past 72 h	✓			✓	✓	✓
Health resource use since last visit^g^				✓	✓	✓
Cost of care^h^						✓
**Blinding success**						
Guess-the-group question for evaluators						✓

*D* day, *M* month, *W* week, *FABQ* Fear, Avoidance, Belief Questionnaire, *EQ-5D-5L* Euroqol Group 5 dimension, 5 level questionnaire

^a^Enrolment visits are performed by recruiting investigators, who are not the same as evaluating investigators

^b^Follow-up visits are performed by evaluating investigators, who are not the same as recruiting investigators

^c^Or just after the end of spa therapy, if applicable

^d^The patient will also be provided with a practical guide on how to manage back pain (the “back book”), including a recommended home exercise programme [15]

^e^Age, sex, duration of current episode of low back pain, signs of spread of osteoarthritis, pain spreading, history of lumbar surgery, need for frequent position changes, bad mood and irritability, sleep disorders due to back pain

^f^Semi quantitative scales that reflect (1) the patient’s and, separately, (2) the physician’s overall opinion concerning the patient’s state of health

^g^Resource use including infiltrations, hospitalizations, physical treatments (massages, traction, physical therapy) and medical imaging of the lumber spine will be tracked

^h^Costs will be estimated using resource-use data gathered during visits and the French National Cost Scale. Indemnities related to days of sick leave will be included in cost estimates

The composition of the spa therapy intervention is based on previous results in the domain. Massage [16–21], heat therapy [20] and water exercises [22] have all been demonstrated as helpful for low back pain. Water exercises in particular have similar efficacy to regular exercise regimens, and are sometimes better tolerated [22]. For the present study, the spa therapy intervention consists of 18 consecutive days of spa therapy (3 weeks of treatment, excepting Sundays), that must occur within 60 days of randomisation (Table 3). The latter will always combine mineral water with physical and hydrotherapeutic treatments, including massages, heat and water exercises: (1) pool activities will be carried out by qualified and trained physiotherapists. Small patient groups (limited to 8–15 patients at a time) will participate in pool sessions with 10 min of free bathing and 15 min of supervised exercises in water at 35 °C; (2) underwater massages on painful areas will be performed by qualified and trained physiotherapists in 10-min sessions with water jets at a temperature of 38 °C; (3) mud applications at a temperature of 45 °C will be performed in 15-min sessions, and will include all painful areas (even outside the lumbar region if necessary). In addition to the latter three criteria, further treatments may be added by consensus of spa practitioners in each spa centre. Patients randomised to the spa therapy arm will be invited by the recruiting investigator to keep trial participation and spa therapy a secret from evaluating investigators. Their participation in spa therapy (observance) will be recorded by spa centre staff.

If required, treatment-stopping for home-exercises will be decided via collaboration between the patient and his/her evaluating doctor. Treatment-stopping may occur for spa-therapy in case of an adverse event, is decided on a case-by-case basis by the on-site doctors overseeing spa-therapy, and does not result in study exclusion.

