### Primary outcome

The primary outcome is the presence/absence of a clinically relevant change (improvement of at least 30%) in the visual analogue scale (VAS) score for pain at 6 months after baseline assessments (see Table 4). This choice is justified by the fact that it is relevant to the patient, figures in international recommendations [35–37], and is qualitative in nature. A qualitative outcome was also preferred because it should minimise the role of placebo effects, which are often significant for quantitative pain variables but not so for qualitative ones [38], and minimise effects associated with a lack of evaluator blinding, as is the case for self-evaluation questionnaires [39]. For the purposes of this study, a clinically relevant change in VAS scores for pain is defined by an improvement of at least 30% [40, 41]; improvements below this value will be considered as treatment failures (absence of clinically relevant change). Cases where patients demonstrate a 30% improvement in VAS scores for pain but nevertheless require hospitalization for back pain during the study follow-up period will also be considered as treatment failures.

**Table 4 Tab4:** Outcome measures

Patient-specific measure	Analysis metric and time frame	Planned analysis type
Number of patients with a clinically relevant change in visual analogue scale (VAS) score for pain, defined by an improvement of at least 30%; cases where patients demonstrate a 30% improvement in VAS scores for pain but nevertheless require hospitalization for back pain during the study follow-up period will be considered as treatment failures (absence of clinically relevant change)^a^	Proportion of patients with clinically relevant change for pain between baseline and 6 months	Comparison of distributions^b^
Huskinsson’s VAS for pain [25]. As recommended by national French health authority standards [26], this will address pain over the last 8 days	Repeated measures at baseline and 1, 6 and 12 months^b^	Mixed model for longitudinal data^c^
The Rolland & Morris (RMDQ) pain scale [27]: in this validated French version [28], a 24-question scale (with scores ranging from 0 (no impact) to 24 (maximum impact)) quantifies the impact of low back pain on daily life		
The Fear Avoidance and Belief Questionnaire (FABQ) assesses inappropriate fears and beliefs concerning back pain; the validated French version will be used [29]		

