The EQ-5D-5L questionnaire [30, 31] will be used to track changes in quality of life. This self-administered questionnaire consists of two pages: the first contains the EQ-5D descriptive system and the second a visual analogue scale. The descriptive system has 5 dimensions (mobility, self-care, usual activities, pain/discomfort, anxiety/depression), each described by 5 levels of intensity (“no problems”, “slight problems”, “moderate problems”, “severe problems” and “extreme problems or complete inability”). The respondent must indicate one intensity level for each dimension	Repeated measures at baseline and 1, 6 and 12 months Proportion of patients with clinically relevant changes according to van der Roer et al. [32] at 1, 6 and 12 months	Mixed model for longitudinal data^c^ Comparison of distributions^b^
Patient Acceptable Symptom State (PASS): yes/no response to the following question: “If you take into account all the activities you have in your daily life, the importance of your pain and your disability, do you consider your condition as satisfactory?” [33]	Proportion of patients with patient-acceptable symptoms at baseline and 1, 6 and 12 months	Comparison of distributions^b^
Overall opinion of the patient on his/her state of health (5-point Likert scale)	Proportion of patients in each state at baseline and 1, 6 and 12 months	Comparison of distributions^b^
Overall opinion of the evaluating physician on the patient’s state of health (5-point Likert scale)		
Daily drug consumption over the past 72 h: • Analgesics (in milligrammes of paracetamol and morphine equivalents) • NSAIDs (reported in milligrammes and as a percentage of the maximum dose) [34] • Corticosteroids (in milligrammes equivalent prednisone) • Benzodiazepine muscle relaxants: % of maximum dose	Repeated measures at baseline and 1, 6 and 12 months	Mixed model for longitudinal data^c^
Number of infiltrations (epidural, posterior articular)	Centrality for the cumulative number of infiltrations at 12 months	Comparison of centrality^d^
Estimated per-patient cost for 1 year of care (based on observations of health resource use throughout the study: drug consumption, hospitalizations, imaging)	Centrality for the cumulative cost of care at 12 months	Comparison of centrality^d^

^a^ The primary outcome

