^b^ The comparison of the number of patients improved (or other proportion) will be performed via distribution comparison tests for independent groups (either the uncorrected χ^2^ test, or Fisher’s exact test if the conditions for the χ^2^ test are not met)

^c^ A mixed model with patients as a random effect and study arm as a fixed effect will be used. A significant time × group interaction would indicate differences in the speed of recovery/change between groups

^d^ Means will be compared using the *t* test for independent groups when variable distributions are normal according to the Shapiro-Wilks test, or otherwise via the Mann Whitney test for comparing medians

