### Recruitment and visits

Recruitment will be assisted by advertising (not mentioning spa therapy) in the local press and by posting information in local pharmacies, physicians’ offices or clinics. In the case of recruitment difficulties, local companies known to have high rates of workers on sick leave for low back pain may be contacted. Following the advertising campaign, telephone contact between responding, potential study participants and a clinical research technician (CRT) will result in referral to a recruiting investigator (depending on location), who is responsible for obtaining consent and for enrolment, baseline evaluations and randomisation. The enrolment visit will start with an initial presentation and provision of informed consent for the UCHE intervention (Table 3). Following presentation of the “back book” and baseline evaluations, participants will be randomised and those allocated to the experimental arm will be invited to sign an additional consent form for spa therapy. As no biological collections or ancillary studies are foreseen in this protocol, further consent procedures beyond the latter are not required. Appointments will be made for spa therapy (in the next 60 days (maximum) for patients consenting to spa therapy in the experimental arm) and for follow-up visits with evaluating physicians for all patients in both arms at months 1, 6 and 12. The specific assessments required at baseline and during follow-up visits are detailed in Table 3 and closely follow the study outcomes plus the following: demographic data and disease history at baseline, home exercise observance and any required harms reporting. No specific post-trial care (beyond routine care) is foreseen.

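### The first follow-up visit is timed by a different rule in each arm, so the secondary month-1 comparisons and the group × time term can mix treatment with time since randomisation

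*Protocol article*

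**What the plan says.** The protocol article times the first follow-up visit in three places.

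- **Table 3** puts visit 1 at M1, with a window of D28–D60. Footnote c adds "Or just after the end of spa therapy, if applicable".
- **Interventions and study arms** describes "18 consecutive days of spa therapy (3 weeks of treatment, excepting Sundays"), "that must occur within 60 days of randomisation". Table 3 gives the intervention period as D1–D60.
- **Recruitment and visits** describes a single schedule, "follow-up visits with evaluating physicians for all patients in both arms at months 1, 6 and 12".

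Table 4 gives look-back periods for two of the measures taken at visit 1. For the pain VAS, "this will address pain over the last 8 days". The drug measure is "Daily drug consumption over the past 72 h". Table 4 states no look-back for RMDQ, FABQ, EQ-5D-5L, PASS or the global opinions, which are also collected at visit 1.

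The longitudinal outcomes go into mixed models. Table 4, note c, states how the interaction will be read: "A significant time × group interaction would indicate differences in the speed of recovery/change between groups". The primary outcome is the "score for pain at 6 months after baseline assessments", and the M6 visit has one ± 4-week window with no arm-specific footnote.

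**The concern.** Footnote c can apply only to someone who has had a spa course. When visit 1 takes place therefore depends on the arm and, within the experimental arm, on whether the patient accepted spa therapy. Three things follow.

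1. Time from baseline at the first follow-up point is set by one rule for spa-takers and by another for everyone else. A trajectory difference at that point may partly reflect different elapsed time, yet the plan reads the interaction as a difference in the rate of change.
2. A visit held just after the course has VAS and drug-use look-back periods that reach into the course. The control value has no corresponding anchor.
3. The footnote and the window do not fit together. A course that starts early is over before D28, and the article does not say which rule then prevails.

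At stake are the secondary month-1 comparisons and the first follow-up point of the repeated-measures analyses. The timing of the visit belongs to the protocol. An analysis plan can model the visit day, but it cannot change which days a patient was asked to recall.

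**Working it through.** The article gives no figure for visit timing by arm, so there is none to reproduce. The sample-size calculation concerns month 6 and does not enter.

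**Step 1. Length of the course.** Input: 18 treatment days, Sundays excluded (Interventions and study arms). A Monday start gives three Monday–Saturday weeks, which is 18 + 2 Sundays = 20 calendar days. Any other start day crosses three Sundays: 18 + 3 = 21 calendar days.

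**Step 2. Possible dates of visit 1 for spa-takers.** Inputs: course confined to D1–D60; visit assumed the day after the last session.

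- Earliest: start D1, end D20–D21, visit D21–D22.
- Latest: end D60, visit D61.
- Controls: D28–D60.

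**Step 3. Share before the window opens.** Assumption: start dates evenly spread over the permitted range (the article gives no distribution).

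- 20-day course: 41 possible starts, visits D21–D61. Those before D28 are D21–D27, so 7/41 = 17.1%. Mean visit day D41.0.
- 21-day course: 40 possible starts, visits D22–D61. Those before D28 are D22–D27, so 6/40 = 15.0%. Mean visit day D41.5.

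**Step 4. Difference in mean visit day.** With the spa mean at about D41, the gap depends on the controls:

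- controls all at D28: spa 41 − 28 = 13 days later;
- controls spread evenly over D28–D60 (mean D44): spa 44 − 41 = 3 days earlier;
- controls all at D60: spa 60 − 41 = 19 days earlier.

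**Step 5. What that could do to the VAS.** Assumptions: underlying improvement with time g(d) = 10 × (1 − 0.5^(d/h)) mm, the same in both arms, with half-life h = 14, 30 or 60 days; spa-takers seen on the last course day, evenly spread over D21–D60 (mean D40.5). The timing effect is mean g(spa dates) − mean g(control dates). A positive value favours spa.

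| | h = 14 | h = 30 | h = 60 |
|---|---|---|---|
| mean g, spa dates | 8.42 | 5.94 | 3.68 |
| g(30) | 7.74 | 5.00 | 2.93 |
| mean g over D28–D60 | 8.74 | 6.29 | 3.95 |
| g(60) | 9.49 | 7.50 | 5.00 |
| **effect, controls at D30** | **+0.69** | **+0.94** | **+0.75** |
| **effect, controls spread over D28–D60** | **−0.32** | **−0.36** | **−0.27** |
| **effect, controls at D60** | **−1.06** | **−1.56** | **−1.32** |

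Effects were computed before rounding. Putting every control at D28, the first day of the window, uses g(28) = 7.50, 4.76 and 2.76 and raises the upper end only to about +1.2 mm (h = 30). For scale, a 30% improvement from the 40 mm entry threshold is 0.30 × 40 = 12 mm.

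**Step 6. Look-back periods.** At a visit the day after a 20–21-day course, the preceding 8 days and the preceding 72 h both lie largely or wholly inside the course. For a control at any date in D28–D60, they cover ordinary usual-care days.

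**The case against.** **The footnote has a purpose.** It keeps patients from being assessed in mid-course. With evenly spread starts of a 20-day course, only 8 of 41 courses (about 20%) would be finished before a fixed D28 visit. An end-of-treatment reading is a legitimate choice. This stands: the problem is not that the spa arm is seen at the end of its course but that controls are not scheduled to match.

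**A reader might infer that the spa arm is measured on treatment.** The text does not support that. The visit comes after the course, and only the look-back periods reach into it. Both arms have the same look-back lengths, and the article states one only for the VAS and drug use, so the recall argument does not extend to every month-1 outcome.

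**A reader might infer a bias in favour of spa therapy.** That requires controls to be seen near D30. Table 3 allows them anywhere in D28–D60, and an even spread turns the sign slightly against spa.

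**A reader might infer that the visit date unblinds the evaluator, with effects carrying on to months 6 and 12.** Most end-of-course dates fall in D28–D60, which is open to both arms. Only a visit before D28 or on D61 would be specific to the spa arm, and the evaluator would need to know the enrolment date and the rule. The article does not say that evaluators know that date. Patients are told not to mention the study at all. Any hint is at most minor.

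**The article is condensed.** It does not say whether time in the mixed models is nominal or actual, and that choice may properly sit in the analysis plan. This stands for the coding of time, but not for the visit rule, which the article itself fixes.

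**Conclusion.** The point holds as a scheduling and labelling fault in secondary analyses. Visit 1 follows an arm-dependent rule: about D21–D61 for spa-takers and D28–D60 for everyone else. The group × time term cannot be read purely as a difference in the rate of change while elapsed time at the first follow-up point is set differently by arm. For the VAS and drug use, the month-1 contrast also sets an immediate end-of-treatment state against an unanchored one.

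The size of the pure timing effect is modest and its sign is unknown: about −1.6 to +0.9 mm on average for controls seen between D60 and D30. That rests on an assumed 10 mm improvement, half-lives of 14–60 days and evenly spread course dates, none of which the article supplies. The 15–17% of spa visits before D28 rests on the same even spread. The D21–D61 range follows from the article's course length and deadline, given a visit the day after the last session and a reading of the 60-day limit as covering the whole course.

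It would be wrong to infer any effect on the main result. The primary endpoint is at 6 months after baseline with a common window, and neither it nor the sample size changes.

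**What to change.** 1. **One scheduling rule for both arms.** Draw each control's visit-1 date from the spa-end dates at the same centre. Draw a date in the same way for experimental-arm patients who decline spa therapy, who have no course end of their own.
2. **Reconcile footnote c with the D28–D60 window.** State a window, common to both arms, that covers every permitted end-of-course date, or say which rule prevails when a course ends before D28. Bring the single-schedule wording in Recruitment and visits into line.
3. **Label visit 1 as an end-of-treatment assessment** in Tables 3 and 4, so that it is not read as a fixed one-month value.
4. **Use actual days since randomisation as time** in the longitudinal models, including for patients already seen, and report the distribution of visit-1 days by arm.

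Item 4 deals with elapsed time only, and relies on the chosen form for time. It cannot undo the look-back mismatch for visits already held.

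Cost: no additional visit, slightly more booking work and a wider spread of control visit dates. The alternative of a single later window for both arms, after the intervention period and clear of the 8-day look-back, would also remove the confounding. It would give up the end-of-course reading, so it is a trade-off and not clearly better.
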